**Fig. 1 Fig1:**
[figure not shown]
Study flow diagram for Altitudes

The study RAs undertaking the follow-up assessments are kept blind to treatment allocation via the following mechanisms: (1) regular reminders are sent to all clinical staff at EPPIC regarding the importance of the blind, (2) at the commencement of each research interview the RA reminds participants of the importance of the blind, (3) study RAs are excluded from all clinically related discussions regarding participants, and (4) the RAs are forbidden from accessing participants’ medical records. The RAs record their best guess of participants’ treatment allocation at 6 months’ follow-up in order to enable an assessment of the success of treatment concealment.

### Interventions

We designed and built Altitudes utilising our MOST software framework which includes three highly integrated functions within one web-based application. These include: (1) online psychoeducation and interactive therapy (divided into specific thematic pathways which are further separated into individual ‘steps’), (2) expert-moderated social networking (via a ‘café’), and (3) peer moderation. The content and functionality of the application was informed by multiple group consultations sessions with carers. Each user can log on at their convenience at any time.

#### The features of the online interactive psychoeducation

The study coordinator inducts new users into Altitudes by orientating them to the system, providing passwords, and highlighting ways to optimise its use and ways to access system help. Users complete, at their own convenience, a series of ‘pathways’ organised into distinct themes including self-care, understanding psychosis, early warning signs and prevention of relapse, understanding their personal strengths as a carer, managing behavioural problems in their relative, and communicating with their relative. In order to maximise the usability of the material, these pathways are comprised of brief thematically related psychoeducation and interactive therapy ‘steps’. The content of these steps has been specifically designed to improve carer stress, e.g. by encouraging self-care, by facilitating carer self-efficacy, and by targeting problematic appraisals known to increase carers’ stress. In addition, the content of the steps have been influenced by social cognition concepts of agency and self-efficacy in family life [42]. The steps and pathways entail regular prompts to users to share their reactions to material with other users through a series of ‘talking points’. To ensure that psychoeducation is translated into meaningful behavioural change, we built specific actions entitled ‘do its’, which are related to therapy content (e.g. to practice mindfulness exercises) and to users’ specific strengths. Users’ comments on steps and completed actions populate the content of the social networking newsfeed. In addition, users are able to indicate their preference for material through ‘like’ buttons, rate the relevancy of content, share content with others users, keep track of which users have completed specific pathways, and identify other users who share their personal strengths. Users can also utilise a ‘team up’ function to indicate their support or join other users in striving for specific behaviour change.

#### The social networking features

Users of Altitudes are encouraged to communicate with each other and with moderators through the online ‘café’ where all other users are visible in the ‘network’ page. Expert moderators (clinical psychologists) are identifiable as a separate class of users within the network. Users can visit the ‘wall’ of fellow users where posts (and comments upon posts) are displayed along with profile information and images uploaded by each user. Moderators can promote specific content within each user’s home page, including suggested actions, which moderators select based upon individual users’ strengths and motivations to use the system. The café menu also includes a group problem-solving function, entitled ‘talk it out’, derived from moderated problem solving as outlined in multifamily therapy research [43]. Users can suggest everyday problems in caring for their relative, and moderators invite other users to join in the ‘problem-solving group’. The system stores previous problems and solutions, providing an easily accessible ‘solution wiki’ to subsequent users. The social networking combined with problem solving and psychoeducation has been designed to provide social support, increase carers’ understanding of their relative’s disorder, and increase flexibility of interpersonal problem solving and communication.

#### Altitudes workshops

Moderators invite users to Altitudes ‘meet ups’, offline face-to-face gatherings held approximately every 6 months during the course of the trial. The Altitudes meet ups are designed to provide users with the opportunity to ask the expert moderators questions and give feedback on the system and encourage increased online interaction between users and moderators of Altitudes.

#### The role of online moderators

Expert moderators, who are clinical psychologists with specialist family work experience, log on to Altitudes at daily intervals with the goal of monitoring safety and encouraging self-care, self-efficacy and positive coping within families by making comments on the newsfeed and sending direct messages to users [42]. Peer moderators, with lived experience of caring for a relative with psychosis, model the use of the system and facilitate online interactions. Moderators present formulations of users at weekly supervision sessions including analyses of system activity and planned interventions to optimise users’ engagement, increase positive affect, and address any specific clinical need by suggesting content matched to users’ interests and needs. Through analytics available on the back-end moderator interface, moderators identify users who are at risk of reduced engagement and form a follow-up plan, which might include prompts to log on or suggestions about the content of Altitudes that matches with the users’ identified needs and interests. Our approach to online moderation was inspired by the Supportive Accountability framework of eHealth interventions, which highlights that human support is critical to ensuring a necessary level of engagement in eHealth systems [44]. Supportive Accountability incorporates self-determination theory, which accounts for individual differences in motivation in terms of the fundamental human needs of relatedness, competency, and autonomy. Moderators develop individualised formulations regarding users’ level of motivation to use Altitudes and how their specific needs can best be addressed to optimise system engagement [45].

#### Specialist family treatment as usual

All trial participants have access to the usual array of services for carers at EPPIC. This includes access to: (1) a series of three group-based, evening psychoeducation sessions entitled ‘Family and Friends’, (2) psychoeducation and support provided by EPPIC outpatient case managers, and (3) specialist family therapist sessions in specific cases, e.g. a brief course of face-to-face family sessions where the young person suffers from a high level of behavioural disturbance.

### Outcome measures

#### Primary outcome

The primary outcome of the trial is carer perceived stress measured by The Perceived Stress Scale (PSS) [46] 3 and 6 months after treatment allocation. The PSS measures perceived stress over the preceding month. The PSS is a valid and reliable 10-item measure rated on a Likert scale ranging from 0 (never) to 4 (very often).

As shown in Table 1, primary and secondary outcomes are measured prior to randomisation and at 6 months’ follow-up. A telephone interview is conducted at 3 months to collect interim ratings on perceived stress by completing The PSS with the participant via telephone. In addition, carers’ momentary appraisals and coping efforts and interactions between carers and their relatives will be tracked over 1 week as they naturally occur in daily life using SEMA, at baseline and 6-month follow-up.

**Table 1 Tab1:** Schedule of outcome measures

	Time point (months)		
Measure	Baseline	3	6
Primary outcomes			
The Perceived Stress Scale	X	X	X
Secondary outcomes			
Hair cortisol	X		X
Centre for Epidemiologic Studies Depression Scale-Revised (CESD-R)	X		X
Penn State Worry Questionnaire (PSWQ)	X		X
Alcohol, Smoking and Substance Involvement Screening Test (ASSIST)	X		X
UCLA Loneliness Scale	X		X
‘Me as a Parent’ Questionnaire	X		X
Ways of Coping Scale (WOC)	X		X
Medical Outcomes Study: Social Support Survey (MOS-SSS)	X		X
Strengths Use Scale (SUS)	X		X
Self-Compassion Scale Short Form (SCS-SF)	X		X
Mindful Attention Awareness Scale (MAAS)	X		X
Satisfaction With Life Scale (SWLS)	X		X
Smartphone Ecological Momentary Assessment (SEMA)^a^	X		X
Family level measures			
The Family Questionnaire (FQ)	X		X
Experience of Care-giving Inventory (ECI)	X		X
The Parent-Adolescent Communication (PAC) Scale	X		X
Subsidiary measures			
AQoL 8D questionnaire	X		X
Resource Use Questionnaire	X		X
Altitudes-specific measures			
Altitudes Perceived Competence Scale	X		X
Altitudes Self-Regulation Questionnaire (A-SRQ)	X		X
Altitudes Health Care Climate Questionnaire (A-HCCQ)	X		X

^a^Smartphone Ecological Momentary Assessment surveys

#### Secondary outcomes

Hair cortisol is a biomarker of chronic stress [47] via long-term alterations in basal hypothalamic-pituitary-adrenal (HPA) axis activity [48]. Mean baseline HPA system activity during the last month is measured by a validated procedure for measuring hair cortisol [48]. A single hair sample (3 cm long, approximately 0.5 cm in diameter) will be collected by the RA from a posterior vertex region on the head. It will be cut from a 0.5-cm patch using scissors as close to the scalp as possible. The hair samples will be wrapped in aluminium foil for protection and stored in plastic tubes. The PSS has been commonly used in conjunction with hair cortisol measurements [49].

Secondary outcomes also include severity of depressive symptoms [50], worry [51], substance use [52], and loneliness [53]. A range of measures tapping into resources to cope with stress include parental self-efficacy [54], coping [55], social support [56], strengths’ use [57], self-compassion [58], and mindfulness [59]. Satisfaction with life will be assessed by the Satisfaction With Life Scale (SWLS) [60].

In order to gain a more dynamic picture of carer stress participants utilise our novel SEMA tool. The SEMA tool is readily downloadable at no charge to participants possessing a smartphone (running Android or iOS operating systems). The tool delivers surveys (administered following the baseline and 6-month assessment time point) at eight time points per day during the waking hours of each participant for a period of 1 week. Participants are prompted to complete SEMA surveys every 90 min (±30 min) over a 12-h period (e.g. 9 a.m. to 9 p.m.) each day for seven consecutive days. SEMA tracks participants’ responses in (near) real time, and ensures minimal loss of data by uploading responses to a secure server or caching responses on the users’ smartphone when an Internet connection is temporarily unavailable. The survey questions include items regarding any interaction with the young person since the last survey (e.g. ‘How much time have you spent interacting with your relative since the last survey?’), perceived behavioural problems in the young person (e.g. ‘My relative has irritated me since the last survey’), attributions for perceived behavioural problems (e.g. ‘I have felt my relative let me down by their behaviour since the last survey’), self-reported coping strategies (informed by our factor analysis of carer coping) (e.g. ‘I have reminded myself that things will work out in the end’) [20], perceived parental self-efficacy at the point of the survey (e.g. ‘During the last interaction, did you handle your relative’s behaviour well?’), perceived stress and depression (e.g. ‘At the moment I feel sad’), and perceived social support (e.g. ‘I have received support or encouragement from others since the last survey’).

Cost-effectiveness as measured by the AQoL 8D questionnaire [61] which allows for the calculation of Quality*-*adjusted Life Years (QALYs) at 6 months’ follow-up. In addition, a Resource Use Questionnaire (RUQ) is used to determine the broader resource use of participants. Additionally, for consenting participants, information regarding utilising of primary health care services will be accessed from Commonwealth Government authorities.

#### Patient and family characteristics

The mental health status of the young person, including their primary and comorbid problems are collected at baseline from carers and is verified against medical records if the young person provides consent.

Carer demographic variables recorded at baseline include age, living situation, years of education completed, employment and marital status, country of birth, and source of income.

Given that families are the unit of randomisation in the current study, relevant family level variables are measured to investigate whether they are independent from individual-level treatment effects. This is especially relevant given the nature of the social networking component of the intervention which may result in interfamily communication effects. Therefore, we include a measure of expressed emotion [62], the impact of the illness on the family [63], and the degree of openness and extent of problems in family communication [64].

#### Altitude-specific measures

Usage of the Altitudes online system is continuously monitored across the study intervention period (i.e. frequency, duration, and patterns of use). In addition, users of Altitudes complete self-report measures of their perceived competence using Altitudes [65], motivations for using Altitudes [66] and their perception of moderation by Altitudes [67].

### Safety

The safety protocol comprises three levels of security including: (1) *system and privacy protection*, (2) *online safety*, and (3) *clinical safety* [68].

The application is hosted on a University of Melbourne web server. The University has standard measures in place to prevent unauthorised access to the server. In addition, the web application includes measures to secure the application and database against unauthorised access. These measures conform to industry best practice as defined by the Open Web Application Security Project [69].

We manage privacy and online safety in accordance with the Australian Communications and Media Authority (ACMA). Temporary or permanent withdrawal from Altitudes is triggered by more than one incident of inappropriate use of the system.

The study coordinator conducts an individual face-to-face induction with Altitudes participants, including details of the terms of use. Altitudes includes a ‘report function’, which enables users at any time to indicate to moderators concerns about any inappropriate material posted by a user. The moderator assesses the basis of the report and responds accordingly, which can include the removal of the material and, in some cases, the deactivation or restriction of the user’s account. In addition, users can ‘switch off’ their profile and hide all of their existing comments on the system should they become concerned about their privacy. If participants do not comply with the guidelines for safe use of Altitudes they can be excluded from the system.

In addition to appropriate use of the system, moderators screen the system daily for evidence of clinical risk, including reports of evidence of deterioration in the mental state of the young person in the care of participants. Where indicated, the moderator conducts a risk assessment based upon available information and advises the participant on appropriate action, including accessing services. The system incorporates visible emergency guidelines and contact information.

Altitudes includes an automated keyword function that is activated each time a participant posts a contribution containing potentially offensive words. The function blocks posts with notifications sent to the user and the Altitudes moderator who can decide to ‘unblock’ the post.

### Data integrity

A custom-built Clinical Trials Management System (CTMS) is used to manage the electronic data of this study. The CTMS includes an electronic Case Report Form (eCRF) and randomisation functionality. The study RAs record participant-level data on a paper-based Case Report Form (CRF). These data are subsequently entered into the eCRF section of the CTMS. The randomisation functionality of the CTMS is used to carry out the randomisation aspect of the study and is operated by the study coordinator. The CTMS is accessed using a secure website and is stored on a secure server. It is designed to maintain the privacy and confidentiality of participant information and to ensure the integrity of the data. Access to CTMS is restricted to study personnel and the level of access is dependent on the person’s role. In particular, the RAs and the investigators do not have access to the randomisation section of the CTMS to ensure that they remain blind. Data are accumulated on three separate secure computer servers, including data collected from the SEMA tool, CTMS and data accumulated from participant activity within the Altitudes online system. Data are also provided from the laboratory analysis of hair samples at the Stratech Scientific APAC laboratory. These various data are aggregated into a single electronic secure databank.

### Statistical analyses and sample size

Between-group differences in the primary outcome will be examined using mixed-model repeated measures (MMRM) which are the preferred methods for the analysis of clinical trial data in psychiatry [70]. Individual time-point measures can be considered to be nested within carers, who may also be considered to be nested within families. MMRM will be used for the analysis of primary and secondary outcome measures. MMRM enables analysis of hierarchically structured data (e.g. allows for violations of assumptions such as homogeneity of regression slopes across time points and effects at the family level) while allowing maximum flexibility in the case of missing data [70].

We have assumed that moderate to large effect sizes will be obtained for the primary outcome of stress. We estimate, based on previous trials including carers at EPPIC, that the cluster size will be small (approximately 1.3) because, in most cases, there will only be one family member involved. An approximate estimate of the intracluster correlation for stress measures is .20. In most cases this would be the two parents/partners which would minimise the influence of genetic effects. In addition, patients’ symptoms account poorly for variance in carer measures of stress, so the estimation of intracluster correlation may even be inflated. Therefore, we estimate that the design effect will be approximately .26.

For continuous measures, if we set *α* at 0.05, a sample size of 64 is required for each of the two groups (total *n* = 128) to achieve power (1 − *β*) of 0.80. A study by Rotondi and colleagues (2010), which included randomisation to a multifamily web-based intervention reported a dropout rate of 3% at the 12-month follow-up, highlighting the acceptability of the design [35]. Taking a more conservative estimate and assuming an attrition rate in the proposed study of approximately 20% at follow-up, we have aimed to recruit 160 family members at baseline to retain 128.

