### Enrolment and randomisation

The recruitment and allocation is depicted in the flow diagram in Fig. 1. The study research assistants (RAs) regularly attend EPPIC clinical team meetings to promote the study. After the RA obtains written informed consent from each family member, families are randomised to Altitudes plus STAU or to STAU alone at a ratio of 1:1. We expect that participant numbers within clusters (i.e. families) are likely to vary from between one and four with a mean cluster size estimate of 1.3. An independent statistician created the randomisation sequence, which includes permutated blocks. The block sizes and randomisation sequence are concealed from the study RAs and investigators. Randomisation occurs after each baseline assessment. When a family member from a newly recruited family provides informed consent and completes the baseline assessment, the study coordinator randomises the family via a secure online Clinical Trials Management System (CTMS). The CTMS sends an automated email to the study coordinator and investigators notifying them of the outcome of randomisation. The study coordinator informs the family of the allocation.

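### The design effect is misprinted as .26 and never applied, so 160 recruits do not give the stated 80% power in a family-randomised trial

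*Protocol article*

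**What the plan says.** Under Enrolment and randomisation, the protocol article makes the family the unit of allocation ("families are randomised to Altitudes plus STAU or to STAU alone at a ratio of 1:1") and expects the number of carers per family to be "likely to vary from between one and four with a mean cluster size estimate of 1.3".

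Under Statistical analyses and sample size, it sets out the following in order:

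- Effect size, in words only: "We have assumed that moderate to large effect sizes will be obtained for the primary outcome of stress".
- Cluster size of about 1.3, because most families will contribute one carer.
- Clustering: "An approximate estimate of the intracluster correlation for stress measures is .20". It adds that this value may be on the high side.
- Design effect: "Therefore, we estimate that the design effect will be approximately .26".
- Sample size: with α at 0.05, "a sample size of 64 is required for each of the two groups" (128 in total) for power of 0.80.
- Attrition of about 20%, which turns 128 retained into 160 recruited.

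No sentence multiplies 64 or 128 by a design effect.

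**The concern.** A design effect is the factor by which clustering multiplies the variance of the treatment comparison. With a positive intracluster correlation it is at least 1. A value of .26 would mean that recruiting relatives from the same family cuts the variance to about a quarter. The printed figure therefore contradicts the two inputs given just before it.

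The second question is whether any design effect, right or wrong, reached the sample size. If it did not, the 80% power belongs to a trial that randomises individual carers, whereas this one randomises families. This is the only justification given for the size of the primary comparison on the Perceived Stress Scale (PSS), so the power claim should follow from the stated inputs.

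**Working it through.** **Inputs from the article.** α = 0.05; power 0.80; 1:1 allocation by family; mean family size 1.3, range 1 to 4; intracluster correlation (ICC) 0.20; attrition 20%.

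**Inputs assumed.** A two-sided test, and d = 0.5. Neither is stated; both are inferred from the 64 per group, as shown next.

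**Step 1: reproduce the plan's sample size.** An unclustered two-sample t-test with d = 0.5, two-sided α = 0.05 and power 0.80 needs 63.8 per group, so 64 per group and 128 in total (power 0.801). Then 128 / (1 − 0.20) = 160. Alternatives do not fit: d = 0.6 gives 45 per group, d = 0.8 gives 26, and a one-sided test at d = 0.5 gives 50 (normal approximation). Solving for d at 64 per group, two-sided, returns 0.499. So 64, 128 and 160 reproduce exactly with no allowance for clustering.

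**Step 2: reproduce the printed design effect.** 1.3 × 0.20 = 0.26. It is mean family size times ICC.

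**Step 3: the design effect on the article's inputs.**

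- Equal clusters: 1 + (m − 1) × ICC = 1 + 0.3 × 0.20 = 1.06.
- Unequal clusters: 1 + (E[m²]/E[m] − 1) × ICC. The article gives the range and mean of family size but no distribution, so those below are assumptions, each with mean 1.3.

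| Share of families with 1 / 2 / 3 / 4 carers (%) | E[m²] | E[m²]/E[m] | Design effect |
|---|---|---|---|
| 70 / 30 / 0 / 0 (least variable possible) | 1.90 | 1.462 | 1.09 |
| 75 / 21 / 3 / 1 | 2.02 | 1.554 | 1.11 |
| 80 / 13 / 4 / 3 | 2.16 | 1.662 | 1.13 |
| 90 / 0 / 0 / 10 (most variable possible) | 2.50 | 1.923 | 1.18 |

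A mean of 1.3 with whole-number sizes cannot give less than 1.09, so 1.06 is the usual textbook approximation and slightly optimistic here.

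**Step 4: what 128 retained carers deliver at d = 0.5.** Effective sample size is 128 / design effect. Carers needed for 80% power are 128 × design effect, and recruits are that figure / 0.80; both are rounded up.

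| Design effect | Effective n | Power | Detectable d at 80% | Retained needed | Recruits needed |
|---|---|---|---|---|---|
| 1.00 | 128.0 | 0.801 | 0.499 | 128 | 160 |
| 1.06 | 120.8 | 0.778 | 0.514 | 136 | 170 |
| 1.09 | 117.2 | 0.765 | 0.522 | 140 | 175 |
| 1.11 | 115.2 | 0.758 | 0.526 | 143 | 178 |
| 1.13 | 113.0 | 0.750 | 0.532 | 145 | 182 |
| 1.18 | 108.1 | 0.731 | 0.544 | 152 | 190 |

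**Step 5: could .26 mean an inflation of 26%?** On the stated inputs the excess over 1 is .06, not .26, so this reading does not match them either. A factor of 1.26 would need 162 retained and 202 recruited, and 128 retained would give power of 0.70. It would not rescue the stated sample size.

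**Step 6: baseline adjustment.** Adjusting for baseline PSS with baseline–follow-up correlation r raises the standardised effect to d / √(1 − r²). At design effect 1.11 and 128 retained:

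- r = 0.3: 0.5 / √0.91 = 0.524, power about 0.80.
- r = 0.5: 0.5 / √0.75 = 0.577, power about 0.87.

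The article states no value of r, so these are illustrations.

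**The case against.** The strongest reply is that the trial may still have 80% power in practice, for four reasons.

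- **Effect size.** The article says moderate to large, and d = 0.5 is the bottom of that range. At d = 0.6, power is about 0.90 at design effect 1.06 and 0.87 at 1.18.
- **Attrition.** The 20% is presented as conservative beside a cited 3%. At 15% attrition, 160 recruits leave 136, which is enough for a design effect of 1.06. At 11% they leave 142, enough for about 1.11.
- **Analysis.** The planned mixed model for repeated measures (MMRM) could gain power from the baseline PSS, as Step 6 shows.
- **ICC.** The article itself says .20 may be too high, and that larger families will mostly be two parents or partners. This favours the low end of the design effects above.

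It is also fair to say that the wrong figure was not used to lower the target, and that the article recognises nesting within families when it describes the analysis. The comparison itself is not threatened.

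These points stand as reasons why the consequence is modest. They do not support the calculation as written. The figure of 64 per group follows only from d = 0.5; at a larger effect it would not be the number required. The 80% is claimed at 20% attrition, with no correlation stated and no baseline adjustment invoked. A high ICC estimate would bring the design effect closer to 1, never below it. Nor can the error be put down to an article condensing a fuller document, because the figure is printed and conflicts with the inputs beside it.

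**Conclusion.** The concern holds. The printed design effect is cluster size times ICC and is impossible with a positive ICC. The inputs give 1.06, or at least 1.09 with whole-number family sizes. No design effect entered the sample size, so the 80% power is that of an individually randomised trial.

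The shortfall is real but small: power is about 0.75 to 0.78 with 128 carers retained, and a worst-case spread of family sizes would take it to 0.73. Equivalently, the effect detectable with 80% power is about 0.51 to 0.53, not 0.50. This rests on d = 0.5 and a two-sided test (both inferred from the 64 per group), ICC 0.20, 20% attrition, no baseline adjustment, and assumed family-size distributions with mean 1.3. The correction should be made because the figure is plainly wrong and underlies the trial's only power statement.

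**What to change.** Revise the sample-size paragraph under Statistical analyses and sample size:

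1. Replace .26 with 1 + (m − 1) × ICC = 1.06, and say that it is about 1.1 when unequal family sizes are allowed for.
2. State that 64 per group assumes d = 0.5 with a two-sided test at 0.05 and no clustering.
3. Restate what 160 recruited and 128 retained provide: power of about 75–78% at d = 0.5, or 80% power to detect d of about 0.51–0.53.
4. If the sponsor prefers to keep the 80% claim at 160 recruits, base it on the MMRM adjusted for baseline PSS, apply the design effect, and state the assumed baseline–follow-up correlation and its source. A correlation of about 0.3 is roughly the minimum needed at a design effect of 1.11.

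The cost is the wording of one paragraph and, unless option 4 is taken, a slightly less favourable power statement. No additional carers, assessments or changes to the analysis are needed; baseline PSS is already collected.
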